## Abstract

**Background:**

Periodontal disease is a chronic state of inflammation that can destroy the supporting tissues around the teeth, leading to the resorption of alveolar bone. The initial strategy for treating periodontal disease is non-surgical sanative therapy (ST). Periodontal disease can also induce dysbiosis in the gut microbiota and contribute to low-grade systemic inflammation. Prebiotic fibers such as inulin can selectively alter the intestinal microbiota and support homeostasis by improving gut barrier functions and preventing inflammation. Providing an inulin supplement prior to and post-ST may influence periodontal health while providing insight into the complex relationship between periodontal disease and the gut microbiota. The primary objective is to determine if inulin is more effective than the placebo at improving clinical periodontal outcomes including probing depth (PD) and bleeding on probing (BOP). Secondary objectives include determining the effects of inulin supplementation pre- and post-ST on salivary markers of inflammation and periodontal-associated pathogens, as these outcomes reflect more rapid changes that can occur.

**Methods:**

We will employ a single-center, randomized, double-blind, placebo-controlled study design and recruit and randomize 170 participants who are receiving ST to manage the periodontal disease to the intervention (inulin) or placebo (maltodextrin) group. A pilot study will be embedded within the randomized controlled trial using the first 48 participants to test the feasibility for the larger, powered trial. The intervention period will begin 4 weeks before ST through to their follow-up appointment at 10 weeks post-ST. Clinical outcomes of periodontal disease including the number of sites with PD ≥ 4 mm and the presence of BOP will be measured at baseline and post-ST. Salivary markers of inflammation, periodontal-associated pathogens, body mass index, and diet will be measured at baseline, pre-ST (after 4 weeks of intervention), and post-ST (after 14 weeks of intervention).

**Discussion:**

We expect that inulin will enhance the positive effect of ST on the management of periodontal disease. The results of the study will provide guidance regarding the use of prebiotics prior to and as a supportive adjunct to ST for periodontal health.

**Trial registration:**

ClinicalTrials.gov NCT04670133. Registered on 17 December 2020.

## Introduction

### Background and rationale {6a}

Periodontal disease is a non-reversible chronic inflammatory disease that is characterized by tissue damage of the supporting structures of teeth including alveolar bone loss. If untreated, tooth loss may result. Key determinants to the initiation and progression include genetic factors, tooth/dentition-related factors, comorbidities (systemic diseases), microbial communities (dental biofilms), and modifiable lifestyle factors (diet and smoking status) [1]. A mainline strategy for treating periodontal disease is non-surgical sanative therapy (ST). This procedure mechanically removes biofilm and calculus that contains pathogenic bacteria using ultrasonic and hand instrumentation. ST is effective at reducing the probing depths in the majority of sites where periodontal disease is present [2, 3] though ST is limited in its ability to remove organisms and calculus in deep periodontal pockets (> 5 mm), furcation areas (bone loss at the base of the tooth where roots meet), as well as within the tissues lining the periodontal pocket [4, 5]. Thus, the underlying causes of inflammation may not be completely eliminated. The effectiveness of ST can be assessed by measuring the changes in clinical outcomes such as probing depth (PD), clinical attachment loss, bleeding on probing (BOP), gingival index, plaque index, furcation involvement, and tooth mobility. However, the new 2017 classification of periodontal disease [6] needs to be taken into account when choosing a primary outcome of evaluating periodontal health. Classification for periodontal disease is now based on a multidimensional staging and grading system. PD is a critical clinical factor involved in determining the staging; the process of classifying the severity and complexity of the periodontal disease. It is also associated with healing after ST [3]. The absence of BOP can serve as a predictor of periodontal stability [7]. Together, both PD and BOP are clinically meaningful outcomes that can be used to determine a patient’s current periodontal status and their response to ST.

There is evidence of a link between our oral and gut microbiota, which is maintained in health and disease. Periodontal-associated pathogens, such as *Porphyromonas gingivalis*, *Prevotella intermedia*, and *Tannerella forsythia* have been found to range from 10^5^ to 10^8^ colony-forming units/mL of saliva in patients with periodontal disease [8, 9]. These bacteria are thought to travel through the proximal regions of the gastrointestinal tract and if they are able to survive the harsh conditions in the stomach, may eventually reach the large intestine [10]. Individuals with periodontal disease were shown to have present lower diversity of their gut microbiomes [11]. *P. gingivalis*, often considered the etiological agent of periodontitis, significantly alters the gut microbiota composition [12]. Changes in gut microbiota were associated with increased concentration of serum endotoxins, increased systemic inflammation, and decreased performances in both glucose and insulin tolerance tests [12]. In humans, the prevalence of severe periodontitis increases with increasing insulin resistance in nondiabetic individuals [13]. Chronic low-grade inflammation, defined as the increased production of pro-inflammatory cytokines and C-reactive protein (CRP), is a critical underlying factor that can contribute to an individual’s periodontal health [14]. A dysbiotic gut microbiota, present in obesity, diabetes, and metabolic syndrome, may be a contributor to this inflammation [15]. Thus, it is plausible that a dynamic loop exists between the oral and the gut microbiota which is altered in inflammatory states and modifiable by interventions targeting the oral and/or gut ecosystems. In summary, a strategy that targets gut bacteria, including prebiotics, may be useful in supporting periodontal health.

Prebiotic administration may be a successful strategy in this context. Prebiotics are defined as substrates that are selectively utilized by host microorganisms conferring a health benefit [16]. Inulin-type fructans are among the most largely substantiated prebiotics. Inulin has a degree of fructose polymerization (DP) between 2 and 60, is undigested by the host, and selectively stimulates gut bacteria. Long-chain (DP = 10–60) inulin supplementation has been shown to lead to an increased production in butyrate, a short-chain fatty acid important in the maintenance of a healthy intestinal epithelium [17, 18]. Prebiotic supplementation and the production of butyrate may help to sustain the intestinal barrier leading to lower serum lipopolysaccharide (LPS) concentrations and improvement of low-grade chronic inflammation (Fig. 1) [19, 20].

**Fig. 1 Fig1:**
[figure not shown]
Possible connection linking periodontal disease, obesity, gut dysbiosis, and low-grade inflammation. Prebiotics may restore the gut microbiome to a state of homeostasis to disrupt the connection

While the effects of inulin supplementation on periodontal disease have not been investigated, epidemiological studies have reported a significant association between intake of dietary fiber and a decreased risk of periodontal disease [21–23]. Aligned with this, higher intakes of fruits and vegetables, including inulin-containing bananas, asparagus, and leeks, were significantly associated with a lower percentage of sites with PD greater than > 3 mm after ST [3]. One intervention study provided individuals with a low-fat, high fiber test meal three times a day for 8 weeks. At the end of the intervention, participants experienced improvements in periodontal disease outcomes that included significant decreases in average PD, clinical attachment levels, and percentage of sites with BOP [24]. Of note is that participants had a body mass index (BMI) of at least 25 kg/m^2^ or demonstrated impaired glucose tolerance—two important risk factors of developing periodontal disease. Although the mechanistic action could not be established in these studies, it is clear that intake of high-fiber foods has benefits for periodontal disease. The main aim of the study is to determine if supplementation with inulin will have beneficial effects on clinical outcomes of periodontal disease in patients with periodontal disease.

### Objectives {7}

The primary objective of this trial is to determine if inulin supplementation for 14 weeks, provided pre-, peri-, and post-ST, is more effective than the placebo at significantly decreasing the mean number of sites with PD ≥ 4 mm and decreasing the presence of BOP. Secondary objectives include determining the effects of inulin supplementation pre-, peri-, and post-ST on salivary markers of inflammation and periodontal-associated pathogens.

### Trial design {8}

A pilot study will be embedded within the randomized controlled trial with the first 48 participants. Once the pilot study is completed and the feasibility has been established, these participants will be included in the full trial. This is a single-center, randomized, double-blind, placebo-controlled study. The flowchart of the study is presented in Fig. 2. Participants will be randomly allocated in a 1:1 ratio into the intervention group (*N* = 85) or control group (*N* = 85).

**Fig. 2 Fig2:**
[figure not shown]
Study design flowchart

The visits and timeline is described below:
Visit 0 (virtual visit): Eligibility screening and informed consent will follow if the participant meets the criteria.Visit I (initial consult): Informed consent (if not given virtually at Visit 0). Randomization to either inulin or placebo group. Baseline periodontal assessment (PD and BOP), anthropometry (weight, height), dietary assessment, salivary markers of inflammation, and periodontal-associated pathogensVisit II (ST is performed): Anthropometry (weight, height), dietary assessment, salivary markers of inflammation, and periodontal-associated pathogens. ST is typically scheduled 4 weeks from the patient’s initial consultation.Visit III (follow-up, post-ST): Final periodontal assessment (PD and BOP), anthropometry (weight, height), dietary assessment, salivary markers of inflammation, and periodontal-associated pathogens.

## Methods: Participants, interventions, and outcomes

### Study setting {9}

Participants will be recruited from a local periodontal clinic. Patients are referred to the specialty clinic by their general dentist or hygienist if they exhibit signs of advanced periodontal disease. Referred patients will be sent an email including the letter of invitation to participate in the study.

### Eligibility criteria {10}

Inclusion criteria include patients of both sexes, attending the clinic with a diagnosed periodontal disease requiring ST and over the age of 19 who are willing and able to provide informed consent.

Exclusion criteria included pregnancy, breast-feeding, demonstrating glycated hemoglobin (HbA1c) levels greater than 8% in the previous 3 months, chronic GI conditions (e.g., colon cancer, inflammatory bowel disease, celiac disease) and infections, use of antibiotics for the management of non-periodontal conditions within the previous 4 weeks, individuals who cannot stop taking laxatives, prebiotics, probiotics, and/or fiber supplements 2 weeks prior to the start of the intervention and for the duration of the study and current smoking and/or cannabis use. Patients with severe periodontal disease that require antibiotics with ST as part of their treatment will be withdrawn. This will be determined after the patients’ initial consultation (Visit I). Patients will also be withdrawn if they do not come back for Visit II or III. The eligibility criteria are summarized in Table 1.

**Table 1 Tab1:** Participant inclusion, exclusion and withdrawal criteria

Inclusion criteria	Exclusion criteria	Withdrawal criteria
· Patients of both sexes attending the clinic with periodontal disease · Over the age 19 (no upper age restriction) · Be able to provide informed, written, or verbal consent	· Demonstrating HbA1c levels greater than 8% in the previous 3 months · Chronic GI conditions (e.g., colon cancer, inflammatory bowel disease, celiac disease) and infections · Current or previous use of antibiotics for management of non-periodontal conditions within the past 4 weeks · Individuals who cannot stop taking laxatives, prebiotics, probiotics and/or fiber supplements 2 weeks prior to the start of the intervention and for the duration of the study · Smokers and/or cannabis users · Pregnant or lactating	· Patients with severe periodontal disease that require antibiotics with ST as part of their treatment · Patients who do not show for Visit II or Visit III

### Who will take informed consent? {26a}

Those that are interested in participating in this study will be invited to a virtual meeting with a member of the research team due to the constraints of the COVID-19 pandemic. Participants can either agree to being virtually recorded as they read the statement from the consent form, fill out the consent form, and send it back via email or bring the consent form with them to their initial consultation (Visit I).

### Additional consent provisions for collection and use of participant data and biological specimens {26b}

A proportion of patients continue at the clinic for long-term/indefinite maintenance of their periodontal health. We may perform a follow-up of the participants after 1 or 2 years or later from the end of this study if they are continuing to have periodontal maintenance appointments at the clinic. If the participant wishes to be involved with the follow-up study, there is a line on the consent form that they can sign.

## Interventions

### Explanation for the choice of comparators {6b}

Participants allocated to the study group will receive inulin (10 g/day; Orafti®GR, Beneo, Mannheim, Germany) while participants in the placebo group will receive maltodextrin (10 g/day; Canadian Protein; Toronto, Ontario, Canada). Maltodextrin is the most common placebo used in intervention studies with inulin because it has a similar physical appearance and energy content to inulin.

### Intervention description {11a}

The supplements will be individually packaged in sachets and will contain 10 g of the specified powder. All participants will be instructed to consume one package per day. Supplements can be mixed with water or with another liquid of choice (250 mL of liquid per serving).

### Criteria for discontinuing or modifying allocated interventions {11b}

Inulin administered at 10 g/day is generally well-tolerated, resulting in only mild gastrointestinal (GI) symptoms of gas/bloating, flatulence, constipation, and GI cramping/rumbling [25]. Furthermore, participants will be instructed to divide the 10 g dose into two 5 g doses—in the morning and evening. This method has been shown to have no significant increase in GI symptom incidence [26]. We believe this will minimize, if any, side effects from the intervention. If the participant cannot continue with the study for any reason, they will be aware they may stop the intervention at any time and it will not affect the level of care they receive at the clinic.

### Strategies to improve adherence to interventions {11c}

All participants will receive exactly 100 sachets to last them until their scheduled follow-up appointment. They will be asked to return any unused sachets when they come in for their follow-up to account for missed dosages. Participants will receive a daily reminder to take the prebiotic in the morning and afternoon using an online application (Auto Message) and will also be instructed to take it prior to brushing their teeth in the morning and at night as an additional reminder.

### Relevant concomitant care permitted or prohibited during the trial {11d}

All relevant concomitant care will be permitted and recorded.

### Provisions for post-trial care {30}

There will be no post trial care. It is anticipated that there will be no risks requiring compensation.

### Outcomes {12}

#### Primary outcome measures

Clinical assessment
Reduction in the number of sites with PD ≥ 4 mmReduction in the presence of BOP

#### Secondary outcome measures

2.Salivary markers of inflammation
Reduction in interleukin-1ß (IL-1ß)Reduction in IL-6Reduction in CRPReduction in matrix metalloproteinase-8 (MMP-8)3.Periodontal-associated pathogens
Reduction in *Aggregatibacter actinomycetemcomitans*Reduction in *Porphyromonas gingivalis*Reduction in *Tannerella forsythia*Reduction in *Treponema denticola*4.Anthropometric parameters
Change in BMI5.Dietary assessment
Change in energy intakeChange in carbohydrate intakeChange in fat intakeChange in protein intake

#### Periodontal examination

All periodontal examinations will be completed by Registered Dental Hygienists with 15 years or more of experience using a periodontal probe. Multiple hygienists will participate in this study and to ensure consistency among measurements, they will be calibrated to apply 25 N of pressure by using an electronic scale [27]. Six PD sites will be measured on all teeth and implants (mesiobuccal, buccal, distobuccal, mesiolingual, lingual, and distolingual) as previously described [27]. The total number of sites with probing depths ≥ 4 mm will be measured. BOP will be measured by visual inspection and expressed as either absent or present at each of the sites.

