#### Sample size for full trial

The number of sites with probing depths ≥ 4 mm was used to determine sample size, as ST has been shown to reduce BOP to minimal levels to the point where an adjunct could not increase the effectiveness [3]. Previous literature has reported the mean change in number of sites with probing depths ≥ 4 mm from baseline to an average follow-up of 10.86 weeks is a mean of 81 with a standard deviation of 21 [3]. It has been shown that a high fiber diet can result in a 4% decrease in average PD though these participants were not diagnosed with periodontal disease and were not undergoing treatment with ST [24]. We believe it is reasonable to estimate that participants who are suffering from this disease and have deeper probing depths will experience a greater reduction in PD ≥ 4 mm in combination with ST (10%), as baseline PD is positively associated with follow-up PD [3]. Thus, the estimated mean change in the number of sites with probing depths of ≥ 4 mm is 91. Using a power of 80% and an alpha of 0.05, the total number of participants needed per group is 71. A 20% drop-out rate is estimated; the sample size for the full trial is 85 per group or a total of 170 participants. The sample size needed for the full trial was estimated using a statistical software (G*Power 3.1).

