## Statistical methods

### Statistical methods for primary and secondary outcomes {20a}

Data will be entered into excel by a member of the research team. Another member will double-check the numbers and values to ensure the accuracy of data entry. Statistical analyses will be performed using IBM SPSS 26 statistical software and significance will be determined when *P* < 0.05. Mean and standard deviations will be reported for outcomes. Analysis of baseline participant demographics will be calculated to ensure consistency between the groups. The Kolmogorov-Smirnov test will be used to test the normality of the data. Levene’s test will be used to assess the equality of variances. Probing depths outcomes will be analyzed using an independent sample *t* test for the mean change in the number of PD ≥ 4 mm. If the data is not normally distributed, a Mann-Whitney test will be used. BOP is a categorical variable and chi-square analyses will be performed to measure the associations between the presence of bleeding and the treatment group.

The concentrations of the four salivary biomarkers and the quantitative values of the four periodontal pathogens at all three sample collection times will be log transformed to normalize their distribution. Two-way repeated measures analysis of variance (ANOVA) using treatment × time will be used to analyze each biomarker and pathogen individually. A repeated-measures ANOVA with Tukey’s post hoc test will be used to determine changes in energy and macronutrient intakes over the 3 visits in the intervention and control groups.

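### Several hygienists chart the primary outcomes, only their probing force is calibrated, and nothing ties a participant's baseline and final charts to one examiner, so avoidable examiner variance can enter the change score

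*Protocol article*

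**What the plan says.** **Who measures.** Under Periodontal examination: "All periodontal examinations will be completed by Registered Dental Hygienists with 15 years or more of experience using a periodontal probe". The same paragraph adds: "Multiple hygienists will participate in this study and to ensure consistency among measurements, they will be calibrated to apply" a set force, checked on an electronic scale. That is the only step it names to keep the hygienists consistent with one another.

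**What is measured.** For probing depth (PD): "The total number of sites with probing depths ≥ 4 mm will be measured". For bleeding on probing (BOP): "BOP will be measured by visual inspection and expressed as either absent or present at each of the sites".

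**When.** The visit list under Trial design {8} puts the "Baseline periodontal assessment (PD and BOP") at Visit I and the final one at Visit III. Section {18a} takes the periodontal data from the clinic's electronic patient files.

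**How it is analysed.** Section {20a} plans an independent-samples t test "for the mean change in the number of PD ≥ 4 mm", with Mann-Whitney if the data are not normal, and chi-square for BOP. No examiner term appears.

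**Planned effect.** Sample size for full trial takes a mean change of 81 sites with SD 21 for sanative therapy alone, and then: "Thus, the estimated mean change in the number of sites with probing depths of ≥ 4 mm is 91". The difference sought is 10 sites.

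**The concern.** The protocol itself raises consistency between examiners, and its answer covers only one source of disagreement. Two hygienists pressing equally hard can still differ in probe angle, probe position and rounding near 4 mm. BOP is a visual call on which examiners can also differ.

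The PD outcome is a within-participant change in a threshold count, so a small systematic reading difference moves several sites in the same direction. If one hygienist does both charts, most of that offset cancels. If two different hygienists do them, both offsets stay in the change. Nothing in the article prevents the second case, and ordinary appointment booking may decide who charts.

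At stake is the precision of the primary comparison. The plan has little slack: its own assumptions give 80.4% power at 71 per group.

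**Working it through.** **1. The plan's own figure.** Inputs from Sample size for full trial: difference 91 − 81 = 10, SD 21, alpha 0.05, power 80%. The standardised effect is 10/21 = 0.476. A two-sided t test needs 70.2, so 71 per group, as stated. Power at 71 is 80.4%.

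**2. Route A: examiner SD expressed in sites.** Let s be the between-examiner SD of the site count and f the fraction of participants charted by two different hygienists. The documents give neither. The variance of the change is 21² + 2·f·s², with full cancellation when one examiner does both charts.

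| f | s (sites) | SD of change | Power at 71 | n per group for 80% |
|---|---|---|---|---|
| 1 | 3 | √(441 + 18) = 21.4 | 78.9% | 74 |
| 1 | 5 | √(441 + 50) = 22.2 | 76.1% | 79 |
| 1 | 10 | √(441 + 200) = 25.3 | 64.7% | 102 |
| 0.5 | 5 | √(441 + 25) = 21.6 | 78.3% | 75 |
| 0.5 | 10 | √(441 + 100) = 23.3 | 72.0% | 86 |

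**3. Route B: examiner SD expressed in mm.** All of these inputs are assumed: 162 sites; true PD about N(4.5, 1.5) mm before and N(3.0, 1.2) mm after therapy; readings rounded to 1 mm, so the effective cut is 3.5 mm; k hygienists assigned at random at each visit, so 1 participant in k is matched by chance.

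- Sites moved per mm of offset = 162 × normal density at 3.5 mm: 34.5 at baseline and 49.4 at follow-up.
- Added variance, different examiners: (34.5² + 49.4²) × SD².
- Added variance, same examiner: (34.5 − 49.4)² × SD².
- The two are mixed with weight 1/k on the matched case and added to 21².

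| Examiner SD | Power, k = 2 | Power, k = 3 to 5 | Power, all matched |
|---|---|---|---|
| 0.1 mm | 79% | 78% | 80% |
| 0.2 mm | 74% | 71–72% | 80% |
| 0.3 mm | 67% | 61–63% | 79% |

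The change SD behind the k = 3 to 5 column is 21.6–21.7, 23.3–23.6 and 25.8–26.6.

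**4. If SD 21 already contains this noise.** Planned power stays at 80%. With k = 4, matching lowers the SD to about 20.4, 18.4 or 14.5 for the three examiner SDs, and power becomes about 83%, 90% or 98%.

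**5. Check of the assumed model.** It puts about 121 sites at or above the cut before therapy and 55 after, a change of about 66. The protocol states 81. Route B is therefore illustrative only.

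**6. Which adjustment works for unmatched charts.** This was simulated under Route B with k = 4, examiner SD 0.2 mm and 71 per group. The SD of the estimated treatment effect was about 3.95 unadjusted, 3.97 with a same-versus-different indicator, and 3.6 with factors for the Visit I and Visit III examiners. The indicator fails because the offset between two examiners has random sign.

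**The case against.** **It is an omission, not an error.** The paragraph states nothing false, uses very experienced hygienists and cites a published method. An article may leave booking practice to operational documents. Part of this stands: the absence of an examiner term in {20a} is not a fault by itself, since covariates are commonly left to the SAP. But the article says that it presents the full protocol, and it positively names force calibration as the means of consistency. Who charts whom is settled before data collection, and a later analysis can use the examiner only if the examiner was recorded. Long experience shows skill, not agreement between examiners.

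**The size rests on assumed inputs.** This stands. The number of sites, the PD distributions, the examiner SD, the number of hygienists and the random assignment are all assumed, and at 0.1 mm the loss is only about 2 points.

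**SD 21 is an observed SD and may already include examiner noise.** This stands. There would then be no shortfall against the plan.

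**Stronger readings that the documents do not support.**
- A reader might infer that the arms are biased. Randomised 1:1 allocation and blinded care providers ({8}, {17a}) point to added variance only.
- A reader might infer that the trial is underpowered. That needs SD 21 to be free of examiner noise, and the documents do not say so.
- A reader might note that, in the assumed model, a 0.2 mm offset moves about 10 sites at Visit III, and equate that with the planned effect. This sets one participant's shift against a difference in group means; the SD between individuals is already 21.

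**Conclusion.** The point holds as a design weakness that is cheap to remove. The protocol uses several examiners, calibrates only their force, and leaves the pairing of a participant's two charts open. Examiner differences can therefore add avoidable variance to the primary PD change. BOP calls are exposed to examiner differences too, but no size was worked out for them.

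The magnitude is conditional. With examiner SDs of 0.1 to 0.3 mm and 2 to 5 hygienists at random, power at 71 per group runs from about 79% to 61% if SD 21 excludes examiner noise. If SD 21 includes it, the planned 80% stands and matching improves precision. The extremes (61% and 98%) both need the largest assumed examiner SD. Matching helps in either case.

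**What to change.** 1. Add to Periodontal examination: for each participant, the same hygienist completes the Visit I and Visit III periodontal charts wherever scheduling allows.
2. Record the examiner at each of the two visits.
3. Keep the planned primary tests. Where charts are unmatched, add a supporting linear model of the PD change with treatment, Visit I examiner and Visit III examiner as factors. Do not use a same-versus-different indicator.

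Cost: a booking constraint at one clinic, one recorded field, and 2(k − 1) degrees of freedom in the supporting model. With four hygienists that is 6 of the 140 residual degrees of freedom available at 71 per group (142 − 2). No extra visits, staff or participants are needed. Some appointments will not be matched; the supporting model is for those.

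### The probing calibration target is printed as a pressure in newtons and equals about 2.55 kg on a scale, so a unit or magnitude slip is likely

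*Protocol article*

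**What the plan says.** The section Periodontal examination explains that several hygienists will examine participants and that their measurements must agree with one another. The means it names for this is a calibration target: "they will be calibrated to apply 25 N of pressure by using an electronic scale". A literature reference follows. The same section asks for hygienists with at least 15 years of experience and for six named sites on all teeth and implants.

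It then defines the two measurements that this probing yields. For depth: "The total number of sites with probing depths ≥ 4 mm will be measured". For bleeding: "BOP will be measured by visual inspection and expressed as either absent or present at each of the sites". Under Primary outcome measures, reductions in these two quantities are the trial's primary outcomes.

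The probing force appears only in that one sentence. No section gives a second force, a probe-tip size, a pressure in pressure units, or a scale reading in grams or kilograms.

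**The concern.** The sentence calls the target a pressure but gives it in a unit of force. If the wording is forgiven and the figure is read as a force, its size is the problem: a reader who follows it would press a periodontal probe on the scale until it showed about two and a half kilograms.

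Both primary outcomes come from this probing. How hard the examiner presses can affect the depth recorded and whether a site bleeds. Depth is counted against a fixed 4 mm cut-off, so a shift in recorded depth can move sites across it. If the printed figure is followed, the level of both outcomes and the comfort of participants are affected. If it is not followed, the target in use is not the one in the protocol, and an outside reader can neither reproduce nor check the calibration.

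**Working it through.** **Inputs from the protocol article.** The target is 25 N, checked on an electronic scale (Periodontal examination). Both primary outcomes come from that examination (Primary outcome measures; Periodontal examination). The sample size rests on a mean change that "is a mean of 81 with a standard deviation of 21" and an assumed 91 with inulin (Sample size for full trial).

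**Inputs not in the article.** Standard gravity is 9.80665 m/s². Probe-tip diameter is an assumption, with a range of 0.4 to 0.6 mm, because the article gives none.

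**Is there a figure of the plan's own to reproduce?** Not for this point. The article derives nothing from the 25 N.

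**Step 1: scale reading.** Mass equivalent = F / g = 25 / 9.80665 = 2.549 kg, or about 2,549 g.

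**Step 2: could the figure work as a pressure?** A pressure needs a force and an area, and the article gives no area. With P = F / (π d² / 4) and the assumed tip diameters, a force of 25 N gives:
- d = 0.4 mm: 25 / 0.1257 mm² = about 199 MPa
- d = 0.5 mm: 25 / 0.1963 mm² = about 127 MPa
- d = 0.6 mm: 25 / 0.2827 mm² = about 88 MPa

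Across the whole range this is implausible for soft tissue probed by hand. The conclusion does not depend on which tip size is assumed.

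**Step 3: how large could a slip be?** As an illustration only, suppose grams and newtons were interchanged. Then 25 gram-force = 0.025 × 9.80665 = 0.245 N, and the printed figure would be off by a factor of about 100 (25 / 0.245 = 102). The article does not say that this happened, and other slips are possible. The calculation shows the order of magnitude at stake; it does not identify the intended value.

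**Step 4: does it reach the sample size?** No. With a difference of 91 − 81 = 10 and an SD of 21, the two-sided t-test calculation at 80% power and alpha 0.05 gives 70.2, which rounds up to 71 per group. That agrees with the article: "Using a power of 80% and an alpha of 0.05, the total number of participants needed per group is 71". The probing force is not an input. Extra variation between examiners would raise the SD above 21 and cost power, but the article gives no basis for saying by how much.

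**The case against.** The strongest reply is that this is a matter of wording. In everyday speech, pressure means how hard one presses. A scale responds to force and its reading converts to newtons by a constant, so pressing a probe on a scale is a workable check. This stands: the instrument and the intended quantity are compatible, and the unit mismatch alone would be trivial. It does not answer the size of the number.

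A second reply is that nothing in the article contradicts the figure. It appears once, and the cited source is not available here. This also stands. The doubt about size rests on physical plausibility and, for the MPa figures, on an assumed tip size.

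A reader might go further and infer three things that the article does not support:
- **That the consistency between hygienists fails.** Agreement needs a common target, not a correctly printed one. If all hygienists were calibrated to the same procedure, a misprinted unit does no harm to their agreement.
- **That this calibration is the only safeguard.** It is the only one expressly labelled as serving consistency, but the experience requirement and the six fixed sites are stated as well.
- **That the treatment comparison is biased.** Allocation is randomised 1:1, participants and care providers are blinded (the hygienists are taken here to be care providers), and probing depth is analysed as change from baseline. A target shared by both arms shifts both alike.

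**Conclusion.** The point holds as a likely slip in the unit or magnitude of a stated operating figure. The unit mismatch and the conversion to about 2.55 kg follow from the text alone. The view that the magnitude is wrong is a strong plausibility argument, not a proof from a second figure in the article.

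The consequence is limited to the level, reliability and reproducibility of PD and BOP and, if the figure is followed literally, patient comfort. There is no evidence that examiners were in fact miscalibrated, and the effect on either outcome cannot be quantified from the article. It is still worth correcting, because the sentence governs the examination that produces both primary outcomes.

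**What to change.** Compare the printed figure with the calibration procedure actually used and with the source cited in that sentence. Then restate the target under Periodontal examination as one consistent quantity and unit, in the form in which it is read on the scale. The sponsor must supply the value from its own record; none is proposed here.

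The cost is one look-up and one corrected sentence. No new procedure, analysis or sample-size calculation is needed. An accepted tolerance can stay in the calibration record; a condensed article need not carry it.
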